#### **7.11. End of Interventional Study Follow-up Visit**

After at least a 1 week and at most 8 weeks washout interval for the interventional study participants will return to the Imperial CRF for routine medical assessment and the following safety assessments will be performed:

- Review concomitant medications
- AE assessment

- Physical examination including vital signs (pulse rate, BP, respiration rate, pulse oximetry and temperature) and assessment of level of disability, using FARS, SARA, SCAFI and speech dysarthria assessment.
- 12-lead ECG in the supine position
- Blood and urine samples will be taken for clinical laboratory assessment (haematology, clinical chemistry, electrolytes, coagulation, fasting lipid profile, enzymes and urinalysis). Blood glucose will be measured using a BM stick. A blood sample for FXN level will also be taken.
- A blood sample for the separate chromatin immunoprecipitation study will be taken.

Participants will be discharged from the interventional study when considered appropriate by the CI.

We do not recommend that participants continue to take nicotinamide post-study as further clinical trials are required to determine whether or not nicotinamide is safe and is of clinical benefit to patients with FRDA. If participants still decide to take nicotinamide against our advice, they will be referred to their GP with recommendation of regular safety follow up to evaluate any nicotinamide-induced toxicity. We may request the FRDA participants consent to come in for visits at the Imperial CRF at the CI's discretion. Blood tests (FXN/chromatin, safety bloods etc) and neurological and medical examinations (SARA, SCAFI, ADL, ECG, vital signs etc) may be performed at these visits.

If the interventional project is successful, FRDA participants may be approached for future research in the same area. It will be entirely up to the participant to decide whether to consent to participation in any future interventional research study.

#### **7.12. Part IV**

A minimum of ten up to a maximum of 20 FRDA participants will be offered the opportunity to participate in Part IV. Up to 20 HVs will also be recruited to participate in this part of the study.

Participants may be contacted by telephone and/or email by the CI or delegates or at their study visit (i.e. FRDA participants participating in the interventional study) to inform them about the potential benefit and any risks associated with participation in this part of the study. fMRI contraindications will be detailed. Participants will be given the PIS and given as much time as they wish to read and ask questions. If the participant wishes to take part, informed consent will be given in writing prior to any study-related assessments being performed. Participants will be assessed for fMRI contraindications during screening (including urine pregnancy test for women of child-bearing potential prior to fMRI) prior to study start.

FRDA participants will undergo the below following assessments over the course of 2 days at the study start, 2 weeks ( $\pm 2$  days), 3 months ( $\pm 2$  weeks) and at 9-12 months ( $\pm 3$  months). In some cases if travel is difficult, participants will be offered overnight accommodation (at the Imperial CRF or private hospital accommodation).

1. Urine pregnancy test only for women of child-bearing potential (prior to fMRI).
2. Blood samples will be taken for:
3. FXN protein estimation by LC-MS/MS compared to the current dipstick assay (Mitosciences);
4. RNA-seq to identify informative biomarkers that might track FXN levels and
5. Analysis of the spatial organisation of the FXN locus by Chromosome-Conformation Capture coupled with high-throughput sequencing (3C-sequencing) to correlate with FXN expression – such a technique may be capable of identifying participants that would be predicted to respond to epigenetic therapies such as nicotinamide.
6. The Edinburgh handedness score will be performed at the study start visit only.
7. Participants will perform standardised tasks derived from the SARA and SCAFI

8. fMRI assessment during the execution of a standardised finger-tapping task (Akhlaghi et al., 2012) and object manipulation. fMRIs will be performed at the Imperial College Centre Imaging Facility (CIF). Participant's hands will be filmed on an fMRI compatible device, which analyses movements in real-time and will be correlated with the fMRI analysis.
9. Participants will be fitted with a simple portable motion-capture device similar to an ECG to be worn overnight. This will be returned the following day.
10. Participants will perform standardised ADL tasks (Appendix 5) and the SARA and SCAFI (not the timed speech test) while wearing a full-body, motion-tracking equipment ('body suit') to capture detailed body kinematics.
11. Participants will perform standardised eye movement tasks to assess the performance of their occulo-motor system quantitatively assessed using a binocular eye-tracking system (optional).
12. Participants will stand on a force plate and their balance performance will be measured (optional).
13. Chromatin immunoprecipitation studies as for Parts II and III to determine longitudinal changes and correlate with FXN expression and clinical phenotype.

Healthy volunteers will come over the course of several visits (not constrained to occur at any point in time, since change in motor behavior is not expected to change significantly for HV during the course of the study) and will perform the following assessments:

1. Urine pregnancy test for women of child-bearing potential only (prior to fMRI).
2. The Edinburgh handedness score.
3. fMRI assessment during the execution of the standardised finger-tapping task (Akhlaghi et al., 2012) and object manipulation. Participant's hands will be filmed on an fMRI compatible device, which analyses movements in real-time and will be correlated with the fMRI analysis.
4. Naturalistic tasks while wearing a motion capture suit and gloves. These include, but are not limited to, naturalistic scenarios (such as "Breakfast" or "Office" scenarios), as well as Repeated Identical Daily Standard Tasks and Clinical Assessments with both the SARA and SCAFI scales.
5. Standardised eye movement tasks to assess the performance of their occulo-motor system quantitatively assessed using a binocular eye-tracking system (optional).
6. Balance performance measurements, by standing on a force plate and performing simple balance control tasks (optional).

## 8. SAFETY

This will be the first use of nicotinamide in participants with FRDA. However, the study is designed with safety and tolerability as outcome measures and draws upon expertise from academia and industry in early phase studies. Nicotinamide will be obtained from an accredited manufacturing source (Teofarma). The safety issues are nausea and isolated reports of reversible abnormal liver function (Knip et al., 2000). Nausea will be monitored throughout by use of a VAS and LFTs measured throughout. A large number of studies have administered nicotinamide at high dose for prolonged periods (Knip et al., 2000). There have been several PK studies where doses of between 6g/day and 9g/day were given to normal volunteers with minimal side effects when given in tablet form (Stratford et al., 1996; Stratford et al., 1992).

Out of a very large number of participants given high-dose nicotinamide only one case of hepatotoxicity has been reported as potentially attributable to prolonged high-dose nicotinamide administration (9g/day) – this was reversible on withdrawal of the drug. No other SAEs have been reported despite high-dose administration for prolonged periods.

### 8.1. Reference Safety Information for nicotinamide

Maximum tolerated dose is the dose above which AEs, likely to be nausea (leading to uncontrolled vomiting), become intolerable and there are biochemical indications of hepatotoxicity (AST, ALT or Bilirubin >25% above the normal range). Nausea will be assessed by VAS (from 0-10). Clearly, if it is severe

enough to cause vomiting which is not relieved by anti-nauseants in more than 50% of participants this will lead to cessation of dose escalation. Overall, the MTD would be exceeded when any of the volunteers had experienced the occurrence of an unexpected, significant or unacceptable AE such that the continuation of the study would put their or other trial participants' safety at risk.

Side effects of nicotinamide and available data on their frequency when using high doses has been reviewed recently by Knip et al (Knip et al., 2000) and are shown in the table below.

**Table 2** Nicotinamide side effects

| Side-effects                    | Reported frequency |
|---------------------------------|--------------------|
| Flushing                        | ≤ 1.5%             |
| Facial erythema                 | ≤ 0.5%             |
| Hives                           | ≤ 0.4%             |
| Sore mouth                      | ≤ 0.4%             |
| Dull headache                   | ≤ 0.5%             |
| Heartburn                       | ≤ 1.6%             |
| Nausea (with radiotherapy)      | 17-65 %            |
| Nausea (without radiotherapy)   | ≤ 1.5%             |
| Other gastrointestinal symptoms | ≤ 0.8%             |
| Inability to focus the eyes     | ≤ 0.4%             |
| Dry hair                        | ≤ 0.4%             |
| Fatigue                         | ≤ 0.4%             |

In addition, further potential effects are hypersensitivity to the nicotinamide preparation used in this study i.e. Nicobion.

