### 1) Single dose escalation study, Part I

Firstly, we will treat the participants with a single dose of 2g of nicotinamide given orally in tablet form. We will measure the FXN levels before treatment and at 2 ( $\pm$  15 mins), 4 ( $\pm$  25mins), 8 ( $\pm$  1hr) and 24 ( $\pm$  2.5hrs) hours after treatment on separated peripheral blood lymphocytes. Plasma will be stored so that nicotinamide concentrations can be assessed by high-performance liquid chromatography (HPLC) as previously described (Stratford et al., 1992). In addition, chromatin will be extracted and stored at  $-80^{\circ}\text{C}$ . In the absence of FXN upregulation we will escalate the dose following a 'flushing out' period of at least one week. We will escalate by 2g increments to 6g and then 1g increments to a maximum of 8g until FXN upregulation is achieved and in the absence of AEs that, in the opinion of the Chief Investigator (CI) or his delegated doctors, may put the safety of the participant at risk. At 8g of nicotinamide we expect that some participants might experience nausea. Participants will be assessed throughout for nausea using a visual analogue scale (VAS). Those with significant nausea will be offered anti-nausea treatment (typically metoclopramide or domperidone) to avoid vomiting. In the event of vomiting occurring, intravenous (IV) fluid will be given as required.

A minimum of ten participants will be recruited in this part of the study according to the schema shown in the table below. Two participants per visit will receive no nicotinamide. This will allow within-participant comparisons and control for the study procedures. The dose escalation will cease when we have reached the maximum tolerated dose (MTD), at least 5-fold upregulation in 50% of participants, or 8g nicotinamide, whatever comes first.

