#### 4.5. Exclusion Criteria for the interventional study

1. Participants with significant clinical dysphagia.
2. Participants taking Sodium Valproate or any other known histone deacetylase inhibitor.
3. Participants taking part in another interventional clinical trial or who have done so within 30 days before screening.
4. Participants known to be positive for human immunodeficiency virus (HIV).
5. Participants with any additional medical condition or illness that, in the opinion of the CI would interfere with study compliance and/or impair the participant's ability to participate or complete the study. Concurrent diseases or conditions that may interfere with study participation or safety include liver disease, bleeding disorders, arrhythmias, organ transplant, organ failure, current neoplasm, poorly controlled diabetes mellitus, poorly controlled hypertension, clinically significant haematological or biochemical abnormality.
6. Patients with a history of substance abuse (e.g. alcohol or drug abuse) within the previous 6 months before enrolment.
7. Participants with a history of severe allergies.
8. Female participants who are lactating or pregnant (positive pre-randomisation serum pregnancy test) or plan to become pregnant during the study.
9. Hypersensitivity to Nicobion (nicotinamide) or any of the excipients in this preparation
10. Liver function tests outside the normal range: aspartate aminotransferase (AST), alanine aminotransferase (ALT), bilirubin which in the opinion of the CI would put the participant's safety at risk.

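### Section 8.1 joins the two limbs of the MTD definition with 'and' where 'or' is needed, so it conflicts with that paragraph's closing rule and the protocol's own account of the risks

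*Protocol*

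**What the plan says.** All the rules stand in one paragraph of Protocol Section 8.1.

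- **Opening definition.** The MTD is the dose above which adverse events, with nausea leading to uncontrolled vomiting named as the likely one, "become intolerable and there are biochemical indications of hepatotoxicity (AST, ALT or Bilirubin >25% above the normal range".
- **Vomiting stop.** Vomiting "which is not relieved by anti-nauseants in more than 50% of participants this will lead to cessation of dose escalation".
- **Closing rule.** "Overall, the MTD would be exceeded when any of the volunteers had experienced the occurrence of an unexpected, significant or unacceptable AE", qualified by "such that the continuation of the study would put their or other trial participants" at risk.

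The introduction to Section 8 treats the two hazards as distinct: "The safety issues are nausea and isolated reports of reversible abnormal liver function".

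The term is used throughout the interventional study:

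- Section 4.1, Part I: "The dose escalation will cease when we have reached the maximum tolerated dose (MTD", or on reaching one of two other limits.
- Table 1: the MTD is one of the doses that D5 can be.
- Section 4.1, Part II: the MTD limits the daily escalation, which is capped at 6 g on days four and five.
- Sections 4.1 and 7.10, Part III: participants dosed in Part II take the MTD already found for them for two months.

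**The concern.** A tolerability threshold with two distinct hazards should be reached when either appears. Written with 'and', the opening sentence is not met by the very event it calls likely, uncontrolled vomiting, unless liver tests are also raised. The 25% limit, which is the protocol's only numeric liver threshold, can never act alone. The closing sentence has no such condition, so the same data can exceed the MTD under one sentence and not under the other. The protocol does not say which prevails.

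What is at stake is the meaning of the dose that ends Part I, can set D5, limits Part II and names the Part III dose. Safety and tolerability are a secondary objective (Section 3.2), and Section 8 describes this as the first use of the drug in the disease. A reported MTD is hard to interpret if the text does not settle which rule produced it.

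**Working it through.** The protocol gives no figure to reproduce here. The check is logical, with one count from the Part I schema.

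**Inputs**
- The three rules in Section 8.1.
- Section 4.1, Part I: "Two participants per visit will receive no nicotinamide". Table 1 lists 10 participants, so 10 − 2 = 8 are dosed at each visit.
- Section 8.2: laboratory abnormalities judged clinically significant count as adverse events.

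**Step 1: four cases.** Let A be an intolerable adverse event and L a liver test more than 25% above normal. The opening sentence is 'A and L'. The closing sentence needs one volunteer with a qualifying event judged to put safety at risk.

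| Case | Opening: A and L | Closing, if judged a safety risk | With 'or' |
|---|---|---|---|
| A only (vomiting, normal liver tests) | not met | met | met |
| L only (isolated liver rise) | not met | met, through Section 8.2 | met |
| A and L | met | met | met |
| neither | not met | not met | not met |

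The opening and closing sentences disagree in the first two rows, which are the two hazards that Section 8 lists separately. If no case is judged a safety risk, those two sentences agree in both rows that the MTD is not exceeded.

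**Step 2: counts for the first case at one Part I visit.** Let k be the number of dosed participants with unrelieved vomiting and normal liver tests.
- Opening sentence: L is false for everyone, so it is met at no k from 0 to 8.
- Closing sentence: met at k = 1 (1/8 = 12.5%), if that case is judged a safety risk.
- Vomiting stop: the smallest count above 50% is 5 of 8 (62.5%), since 4 of 8 is exactly 50%. If all 10 participants are the denominator it is 6 of 10 (60%). The protocol does not say which denominator is meant.

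**Step 3: does the vomiting stop add a second contradiction?** No. It says that more than 50% is enough to stop, not that it is needed. One safety-threatening event is also enough. No data set makes one of these rules say stop while the other says continue. The conflict lies between the opening definition and the closing sentence. At k = 8, for example, escalation has stopped, yet the MTD as defined in the opening sentence has not been passed.

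**Step 4: is a simple 'or' enough?** Not quite. Item 10 of Section 4.5 begins "Liver function tests outside the normal range: aspartate aminotransferase (AST), alanine aminotransferase (ALT), bilirubin which in the opinion of the CI would put the", so exclusion turns on how the CI views the risk to that person and not on the result alone. Someone with raised tests that the CI does not judge a risk can therefore enter. A bare 'or' could place such a person above the MTD before any dose, so the liver limb must refer to a rise from a pre-dose value.

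**Step 5: individual or cohort?** Part II speaks of the MTD being reached in one or more participants, and Part III of each participant's own MTD. The closing sentence of Section 8.1 and the Part I stop act on the whole study. The corrected text has to keep these levels apart. Otherwise a single liver rise would reach the MTD by definition while the cohort rule let escalation continue.

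**The case against.** The strongest reply is that 'and' is loose drafting and that the closing sentence, which begins with 'Overall', is the operative rule. Part II supports this: its examples of events to prevent once the MTD is reached are excessive nausea and vomiting, with no liver condition. That reading is plausible and probably the intended one. The text does not state it, though, and the opening sentence is the one worded as the definition.

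The second reply is that practice would change little. Parts I and II allow escalation only in the absence of events that the CI or delegates judge a safety risk. In Part III the same CI judgement governs escalation and dose adjustment. Section 8.2 brings a clinically significant liver abnormality within the closing sentence. All of this stands, and it limits how serious the point is.

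Three stronger readings are tempting but unsupported:

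- **That participants are left unprotected or would be overdosed.** The judgement clauses apply in every dosing part, whatever the wording of Section 8.1.
- **That 5 of 8 against 1 of 8 is itself a contradiction.** Those are two compatible triggers, each sufficient alone.
- **That Part III escalation has no upper limit.** The sentence for participants escalated within Part III names none, but Section 5.4 sets the study range at 2 g to 8 g daily. A 6 g ceiling for them would be a new restriction, not a correction of wording.

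**Conclusion.** The point holds as a wrongly worded threshold that should be fixed. Read literally, the opening definition is not met by either of the two hazards the protocol names when it occurs alone. For vomiting with normal liver tests it is met at 0 of the 9 possible counts (0 to 8 dosed participants), while the closing sentence is met at 1.

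This rests on three things: a literal reading of 'and', the ten-participant schema in Table 1, and the event being judged a safety risk for the closing sentence to apply. Table 2 gives reported side-effect frequencies, but the protocol gives no rate for unrelieved vomiting or for liver rises above 25% at these doses. No probability is therefore attached. Confidence is medium, because the intended meaning can probably be guessed.

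A smaller wording point follows. Part II is capped at 6 g, so a participant who tolerates 6 g has no MTD in the Section 8.1 sense to carry into Part III.

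**What to change.** 1. In Section 8.1, replace 'and there are' with 'or there are treatment-emergent' before the biochemical limb. Keep the 25% limit, and require a rise from the participant's last sample before the first nicotinamide dose.
2. State that meeting either limb sets that participant's own MTD, and that this participant is not escalated further. This matches how Parts II and III already use the term.
3. State the cohort rule separately. Escalation stops for everyone if any volunteer has an adverse event judged to put safety at risk, or if more than 50% of dosed participants have unrelieved vomiting. Naming dosed participants settles the denominator. Make clear that the Part I stop in Section 4.1 refers to this cohort rule.
4. In Sections 4.1 and 7.10 (Part III), say that the MTD carried over is the participant's highest tolerated Part II dose, which Part II caps at 6 g. Add no new ceiling for participants escalated within Part III.

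The cost is a few lines of amendment. No extra samples are needed: liver tests are already taken at screening, before dosing and at 24 hours in Part I (Section 7.6), daily before dosing in Part II and weekly before dosing in Part III (Section 7.10). The downside is that an individual's escalation may stop slightly earlier.

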## 8.2. Adverse Event Terminology / Definition

An AE is “any untoward medical occurrence in a participant to whom a medicinal product has been administered, including occurrences which are not necessarily caused by or related to that product”. An AE can therefore be any unfavorable and unintended sign (including an abnormal laboratory finding), symptom, or disease temporally associated with the use of an investigational medicinal product (IMP), whether or not considered related to the IMP.

AEs include any of the following:

- Worsening (change in nature, severity or frequency) of conditions present at the onset of the trial
- Participant deterioration due to the primary illness
- Inter-current illnesses
- Drug interactions
- Events related or possibly related to concomitant medications
- Abnormal laboratory values or changes of vital signs, as well as significant shifts from baseline within the range of normal, which the CI or delegates considers to be clinically significant (CS)

### 8.3. Adverse Drug Reaction

In the pre-approval clinical experience with a new medicinal product or its new usage, particularly as the therapeutic dose(s) may not be established, an adverse drug reaction (ADR) is defined as: 'Any untoward and unintended response in a participant to an IMP which is related to any dose administered to that participant.

#### 8.3.1. Unexpected Adverse Drug Reaction

An unexpected ADR is an ADR, the nature or severity of which is not consistent with the applicable product information, also known as reference safety information (RSI). The RSI for nicotinamide is found in section 8.1.

